### Planned statistical analyses

2.14

Intention-to-treat analyses in each group will be performed, and survival curves will be estimated with Kaplan-Meier method. A log-rank test will be used to evaluate differences in the survival curves between the two groups of patients. Hazard ratio will be estimated with the Cox proportional hazard model. Restricted mean survival time will be considered to quantify the treatment benefit in the absence of proportional hazard assumption in survival curves. ORR (CR + PR) and DCR (CR + PR + SD) in each group using the best response evaluated by RECIST v1.1 will be estimated for 95% confidence interval with Clopper-Pearson method. AEs in each group will be aggregated by grades and types, and the proportion of AEs will be compared between the groups by Fisher's exact test. The chronological changes in the HRQOL from the baseline evaluation using EORTC QLQ-C30, FKSI-DRS, and EQ-5D will be compared. All the tests will be two-sided, and a *P*-value of 0.05 will be considered statistically significant.

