### Methods of recruitment and random allocation

2.7

Recruitment was from October 2013 to September 2017. Eligible patients were randomly assigned to one of two treatment groups through the data center at the Innovative Clinical Research Center Kanazawa University (iCREK). Randomization was centrally performed by Waritsukekun (Mebix, Tokyo, Japan) using stratified sampling method to obtain adequate between-group balance for age (<70 or ≥ 70), MSKCC risk (favorable or intermediate), status of metastasis (lung only or other than lung), and participating institution.

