### Sample size consideration and anticipated completion of enrollment

2.13

Based on the AXIS trial (second-line axitinib versus sorafenib) reported by Rini et al. [2] and the reports from Akaza et al. [11], the median total TTF would be calculated as 26.1 (10.4 + 15.7) months for combination of INFα + IL-2 and axitinib, and 15.3 months (10.5 + 4.8) for the combination of sunitinib and axitinib. In this study, hypothetical median TTFs were set for 26 months in the combination of INFα + IL-2 and axitinib and 15 months for the combination of sunitinib and axitinib. We calculated the sample size from the study duration of 5 years (two-year entry period and three-year observation period) and the difference in total TTF between the groups. To detect a significant difference between the groups by a log-rank test with significant level of 0.05 and power of 80%, at least 65 patients in each group are required. Furthermore, given the assumption that approximately 10% of randomized patients will not be evaluated for various reasons, the target sample size was set at 72 patients per group (total 144 cases).

The final patients were enrolled in September 2017, and the entire study will be completed by September 2020.

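### Randomisation is stratified on four factors, but the stated log-rank test and Cox model use none of them; the test stays valid but may lose some power

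*Protocol article*

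**What the plan says.** Section 2.7 (Methods of recruitment and random allocation) describes central randomisation stratified to obtain "between-group balance for age (<70 or ≥ 70), MSKCC risk (favorable or intermediate), status of metastasis (lung only or other than lung), and participating institution". That is three patient factors with two levels each, plus institution. The allocation algorithm is not given.

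Section 2.14 (Planned statistical analyses) specifies an intention-to-treat analysis with Kaplan-Meier curves. For the comparison it states "A log-rank test will be used to evaluate differences in the survival curves between the two groups of patients", and for the effect estimate "Hazard ratio will be estimated with the Cox proportional hazard model". No strata or covariates are attached to either, and neither is labelled unstratified or unadjusted. The section is otherwise fairly specific: it names Clopper-Pearson intervals, Fisher's exact test, restricted mean survival time if hazards are not proportional, and two-sided testing at 0.05.

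Section 2.13 (Sample size consideration) bases the trial size on a log-rank comparison: "by a log-rank test with significant level of 0.05 and power of 80%, at least 65 patients in each group are required".

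**The concern.** Stratified allocation makes the arms more alike on the stratification factors than chance would. If those factors predict outcome, a log-rank test that ignores them still uses a variance that includes the between-stratum differences, which the design has already balanced out. The test then rejects less often than it could. A treatment-only Cox model also estimates a marginal hazard ratio, which lies nearer 1 than the within-stratum one.

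Of the factors, MSKCC risk is the one whose prognostic role the article supports most directly. It is a risk classification used for eligibility, and the Introduction and Discussion link both response to cytokines and recommended treatment to it.

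With 144 patients and a target of 80% power, a few points matter. There are also several defensible versions of the primary analysis: unstratified, four strata, eight strata, or with institution included. If none is fixed in advance, the choice could be made after the results are seen, in an open-label trial.

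**Working it through.** **1. Reproduce the planned size.** The inputs are from section 2.13: "hypothetical median TTFs were set for 26 months in the combination of INFα + IL-2 and axitinib and 15 months" in the sunitinib sequence, and a "study duration of 5 years (two-year entry period and three-year observation period".

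- Hazard ratio under exponential survival: 15/26 = 0.577.
- Events (Schoenfeld, two-sided 0.05, 80% power): 4 × (1.960 + 0.842)² / (ln 0.577)² = 4 × 7.849 / 0.3026 ≈ 104.
- Event probability per arm: 1 − [exp(−λF) − exp(−λ(A+F))]/(λA), with λ = ln 2/median, A = 24 and F = 36 months. The average over the two arms is 0.801.
- Patients: 104/0.801 ≈ 130, or 65 per group.

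The stated 65 reproduces from an unstratified log-rank formula.

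**2. Assumptions for the rest.** The article gives no prognostic hazard ratio and no stratum prevalence. I assumed prevalences of 0.30 to 0.35 (age), 0.5 (MSKCC risk) and 0.5 (metastatic site), exponential times, a within-stratum treatment hazard ratio of 0.577 and allocation balanced within the eight cells of the three patient factors. The prognostic effects are varied from none to strong. Each simulated scenario in the two tables has 6,000 replicates, so the simulation error on a power near 80% is about √(0.8 × 0.2/6000) = 0.5 points.

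**3. The planned 130 patients, unstratified versus eight strata.**

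| Prognostic HRs (age/MSKCC/site) | Power, unstratified | Power, 8 strata | Change | Cox HR, unstratified | Cox HR, 8 strata |
|---|---|---|---|---|---|
| 1/1/1 | 80.5% | 77.4% | −3.1 | 0.574 | 0.572 |
| 1.1/1.5/1.3 | 77.3% | 76.4% | −0.9 | 0.587 | 0.575 |
| 1.2/2.0/1.5 | 73.3% | 76.2% | +2.9 | 0.602 | 0.572 |
| 1.3/2.5/2.0 | 64.4% | 73.7% | +9.3 | 0.630 | 0.575 |

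**4. The target 144 patients, with the actual calendar (4 years of recruitment plus 3 years), adding a four-stratum version (MSKCC risk × site).**

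| Prognostic HRs | Unstratified | 8 strata | 4 strata |
|---|---|---|---|
| 1.1/1.5/1.3 | 82.5% | 81.8% | 83.1% |
| 1.2/2.0/1.5 | 78.9% | 82.7% | 83.9% |
| 1.2/2.5/1.8 | 73.3% | 81.1% | 82.7% |

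With no prognostic effect, a separate run gave 87%, 83% and 86%. So eight strata cost about 4 points in that case and four strata about 1.

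**5. Type I error of the unstratified test (144 patients).** With balance within eight cells it was 4.9% with no prognostic effect, 4.5% with mild effects, 4.1% with moderate (1.2/2.0/1.5) and 3.6% with strong (1.2/2.5/1.8); the eight-stratum test stayed at 4.7 to 5.4%. A smaller run (3,000 replicates) gave 3.6% (moderate) and 3.0% (strong). When institution was also crossed into the allocation (20 institutions and blocks of 4 assumed), these became 4.6% and 4.7%.

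**6. Institution as an analysis stratum.** Twenty assumed institutions × 8 cells = 160 cells for 144 patients. In simulation with 130 patients, the power of that analysis fell to about 24 to 27%.

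**The case against.** The strongest objection is that the gap is read from silence. A journal article condenses the protocol, strata and covariates are often left to an analysis plan, and nothing in sections 2.7, 2.13 and 2.14 is false or contradictory. This limits the certainty: the full plan may already stratify. It does not remove the point, because section 2.14 states the test and the model in otherwise specific terms, and on its ordinary reading that analysis leaves out factors the design used.

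The second objection is that the size rests on assumed prognostic effects. This stands in full. With none or mild effects, an eight-stratum analysis gains nothing and can lose 1 to 4 points.

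A reader might also infer several stronger things that the documents do not support:

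- **That the primary test is invalid or raises the false-positive risk.** It does neither; any error is on the conservative side.
- **That its true type I error is 3 to 4%.** That depends on the allocation algorithm, which the article does not give, and on leaving institution out. With institution crossed in, the figure was close to 5%.
- **That the unstratified hazard ratio is wrong.** Marginal and within-stratum hazard ratios are both legitimate quantities. The marginal one simply lies nearer 1.
- **That stratifying would show whether the effect differs between favorable and intermediate risk.** A stratified test still gives one pooled effect.
- **That eight strata would be the analysis as randomised.** Institution is a fourth factor and cannot sensibly be carried over.

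**Conclusion.** The point holds as a modest efficiency and pre-specification issue. The design stratifies on four factors, and the stated primary analysis uses none. If MSKCC risk and metastatic site are at least moderately prognostic (assumed hazard ratios of about 2.0 and 1.5 or more), the unstratified test loses about 3 to 9 points of power. Its Cox estimate would be about 0.60 to 0.63, against a within-stratum 0.577. If the factors are weak, there is no loss. It would go too far to say that the plan definitely wastes power, since no figure in the article establishes the prognostic effects. The sample size of 65 per group does not depend on this point.

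**What to change.** Before the data are analysed, state that the primary log-rank test and the Cox model are stratified by MSKCC risk (favorable or intermediate) and metastatic site (lung only or other), giving four strata. Age group may be added as a further stratum or as a Cox covariate, provided the choice is fixed in advance. Say explicitly that institution is not an analysis stratum, because the cells would be too sparse. Keep the unstratified test and hazard ratio as a sensitivity analysis. If the analysis plan already specifies this, confirming it is enough.

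The cost is a sentence or two. The factors were needed for allocation, so no new data are required. The statistical downside is about 1 to 3 points of power if the factors prove not to be prognostic, or up to about 4 with eight strata.

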### Administration of IFNα plus IL-2 vs. first-line therapy with sunitinib followed by second-line with axitinib

2.8

Patients assigned to cytokine group receive intravenous injection of IL-2 at a dose of 700,000 unit/day five days/week for the initial 2 or 4 weeks, and then, one or three times/week as maintenance plus subcutaneous injection of IFNα 5–6 million units two or three times/week (Fig. 2). Sunitinib at a dose of 50 mg/day is orally administered to patients who are assigned to the sunitinib group, and one course consists of 4 weeks of administration and 2 weeks of withdrawal. A schedule of 2 weeks of administration and one week of withdrawal is also permitted. Reduction of doses is permitted if a clinical investigator considers the basic doses inappropriate for any reason. The administration of IL-2 plus IFNα or sunitinib is terminated when progressive disease (PD) is confirmed based on RECIST v.1.1, the patient dies, or severe AEs occur. A clinical investigator administers axitinib as second-line treatment immediately after confirmed comprehensive evaluation of PD based on RECIST v.1.1 during first-line treatment. In case of cessation of first-line treatment because of severe AEs, a clinical investigator may consider restarting first-line treatment after recovery below grade 2. Axitinib at a dose of 10 mg/day (5 mg dose twice per day) is orally administered to patients as second-line treatment. Dose reduction or dose increase up to 20 mg/day (10 mg dose twice per day) is permitted if a clinical investigator considers the basic doses inappropriate for any reason. The administration of axitinib is terminated when PD is confirmed by comprehensive evaluation based on RECIST v.1.1, the patient dies, or severe AEs corresponding to discontinuation criteria occur. Zoledronic acid and denosumab are permitted for patients with bone metastasis.

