### Seven secondary endpoints are set in the ESCAPE study

2.11

1.OS, defined as the time from randomization to death from any cause.2.Each PFS in first-line treatment and second-line treatment based on RECIST v.1.1 criteria.3.Objective response rate (ORR), defined as the proportion of CR and partial response (PR) cases in total cases based on best overall response using RECIST v.1.1 criteria, and disease control rate (DCR), defined as the proportion of CR, PR, and stable disease (SD) cases in total cases in first-line and second-line treatment.4.Time to treatment failure (TTF), defined as the time from commencement of first-line therapy to earliest time of PD using RECIST v.1.1 criteria, death from any cause, or cancellation of therapy in first-line treatment.5.Total TTF from first-line to second-line treatment, defined as the time from commencement of first-line therapy to earliest time of PD using RECIST v.1.1 criteria, death from any cause, or cancellation of the therapy in second-line treatment.6.Safety in first-line and second-line treatment evaluated by Common Terminology Criteria for Adverse Events v4.0 system.7.HRQOL in first-line and second-line treatment evaluated by EORTC QTQ-C30, FKSI-DRS, and EQ-5D.

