Each ORR of axitinib as second-line after sunitinib as first-line and after cytokine as first-line treatment was 11.3% and 32.5%, and each PFS was 4.8 months and 12 months in the AXIS trial, respectively. Therefore, axitinib was more effective after cytokine than after sunitinib [2]. Escudier et al. reported that each ORR of sorafenib 800 mg as second-line after disease progression using cytokine as first-line and sorafenib 1200 mg as second-line after disease progression using sorafenib 800 mg as first-line treatment was 20% and 5.2%, respectively. Namely, sorafenib was more effective after cytokine than dose escalation [24]. Moroto et al. reported that each excellent ORR and DCR of sorafenib after 6- or 12-week administration of combination of IFNα and IL-2 was 44.4% and 94.4%, respectively [25].

In some cases of mRCC, especially in Japanese patients whose response to cytokine therapy would be good, the duration of response by the first-line cytokine and second-line TKI could be longer than that of first-line TKI treatment and second-line treatment with another agent. Conversely, AEs of sunitinib in Japanese patients tend to be more severe than in Westerners; therefore, management for the AEs of sunitinib is sometimes difficult, even though we had accumulated experience of AEs with sunitinib. To improve the outcome of sequential treatment for mRCC, we planned a prospective randomized controlled open-label trial between first-line IFNα + IL-2 and second-line axitinib and first-line sunitinib and second-line axitinib, which is considered as a standard first- and second-line treatment for patients with mRCC with favorable risk. Our expectation of this trial is it will clarify better first- and second-line sequential treatment for mRCC, especially in patients with favorable risk and some patients with intermediate risk. In doing so, the results of the trial will definitely contribute to new information for the strategy of first- and second-line sequential treatment for patients with mRCC.

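### Second-line AE comparison: Fisher's test on crude proportions can show excess axitinib toxicity after cytokines at equal monthly risk, because the design assumes 2.5 to 3.3 times longer axitinib treatment in that arm

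*Protocol article*

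**What the plan says.** Planned statistical analyses (2.14) fixes the method: "AEs in each group will be aggregated by grades and types, and the proportion of AEs will be compared between the groups". The named method is Fisher's exact test, and the same section makes all tests two-sided at 0.05. The article does not mention time at risk in connection with AEs.

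The secondary endpoints (2.11) include "Safety in first-line and second-line treatment evaluated by Common Terminology Criteria for Adverse Events v4.0 system", so the comparison is wanted for each line.

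The treatment section (2.8) gives axitinib to both arms as second line and continues it until progression, death or qualifying severe AEs: "The administration of axitinib is terminated when PD is confirmed by comprehensive evaluation based on RECIST v.1.1, the patient dies" is the opening of that rule.

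The sample size section (2.13) builds its assumptions from the two lines. For the cytokine sequence it states that "the median total TTF would be calculated as 26.1 (10.4 + 15.7) months for combination of INFα + IL-2 and axitinib". In the other arm, the corresponding figure is given as "15.3 months (10.5 + 4.8) for the combination of sunitinib and axitinib". The Discussion gives another figure for axitinib by prior therapy (after sunitinib, then after cytokine): "each PFS was 4.8 months and 12 months in the AXIS trial, respectively".

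**The concern.** The planned advantage of the cytokine sequence lies almost entirely in second line. The first-line medians are practically equal, and the axitinib component is much longer after cytokines. Patients who stay on a drug longer have more time to develop an AE. If the efficacy hypothesis is true, the crude second-line proportion with an AE can therefore be higher in the cytokine arm even when axitinib is equally toxic per month in both arms. The better the sequence works, the worse its second-line safety can look.

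The trial's stated aim covers efficacy and safety. A significant p-value for second-line AEs could be read as poorer tolerability of axitinib after cytokines when it reflects longer treatment.

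**Working it through.** **Inputs from the article.** Axitinib medians: 15.7 against 4.8 months (2.13) or 12 against 4.8 months (Discussion). First-line medians: 10.4 against 10.5 months. Design medians for the whole sequence: 26 against 15 months. Evaluable patients: 65 per group.

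**The plan's own figure.** The article gives no power or error rate for the AE comparison. Its sample size does reproduce. With hazard ratio 15/26 = 0.577, 80% power and two-sided 0.05, Schoenfeld's formula gives 4 × (1.960 + 0.842)² / (ln 0.577)² ≈ 104 events. Exponential survival with 24 months of entry and 36 months of further follow-up gives event probabilities of 0.717 and 0.886, mean 0.801. Then 104 / 0.801 / 2 = 64.9, so 65 per group. Note that 65 is the whole evaluable group, not the number reaching axitinib.

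**Exposure ratios.** Second line: 15.7/4.8 = 3.27, or 12/4.8 = 2.5. First line: 10.4/10.5 = 0.99. Whole sequence: 26/15 = 1.73.

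**Persistent risk, second line.** Assumptions, not in the article: AE hazard h constant and equal in both arms, time on axitinib exponential, and 65 or 45 patients per arm starting it. Then P(AE) = h / (h + ln 2/median). For h = 0.05 and median 15.7: 0.05 / (0.05 + 0.0441) = 0.531. For median 4.8: 0.05 / (0.05 + 0.1444) = 0.257. The rejection probability is summed exactly over binomial outcomes.

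| h per month | Medians (months) | Expected % with AE, cytokine vs sunitinib arm | Fisher significant against cytokines, 65/arm | 45/arm |
|---|---|---|---|---|
| 0.01 | 15.7 vs 4.8 | 18.5 vs 6.5 | 45% | 30% |
| 0.01 | 12 vs 4.8 | 14.8 vs 6.5 | 24% | 15% |
| 0.02 | 15.7 vs 4.8 | 31.2 vs 12.2 | 70% | 50% |
| 0.02 | 12 vs 4.8 | 25.7 vs 12.2 | 43% | 28% |
| 0.05 | 15.7 vs 4.8 | 53.1 vs 25.7 | 87% | 70% |
| 0.05 | 12 vs 4.8 | 46.4 vs 25.7 | 64% | 46% |

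Significance in the opposite direction is essentially nil throughout.

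**Where the effect fades.** If the hazard acts only in the first T months of axitinib, P(AE) = h/(h + μ) × (1 − exp(−(h + μ)T)), with μ = ln 2/median. With h = 0.3 and medians 15.7 and 4.8, T = 1 gives 25.4% against 24.2% (about 2% rejection against cytokines), and T = 3 gives 56.1% against 49.7% (about 8%). In first line the expected proportions are practically equal, with 1–2% rejection in each direction. Over the whole sequence, with h from 0.005 to 0.3, rejection against cytokines is 10–28%.

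**Behaviour of alternatives at equal toxicity.** Under a constant hazard, first events per patient-month with a Wald test on the log rate ratio gave a median ratio of 1.00–1.03 and 3–5% rejection (65 per arm, 4,000 simulated trials per scenario). When AEs occur only in the first one to three months, the same rates gave ratios of about 0.3 to 0.5 and falsely favoured cytokines in 53–86% of simulated trials. A log-rank comparison of time to first AE, censored at the end of axitinib, held 3–6% error in every scenario.

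**The case against.** Crude incidence by grade and type is a conventional and legitimate summary. It is the share of patients harmed while on the planned sequence, and more AEs from longer treatment are a real burden. This stands as a reason to keep the table. It does not make the test on that table a comparison of axitinib's toxicity between arms.

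The article condenses a fuller protocol, and an unseen analysis plan may add exposure-adjusted analyses. That is fair, and their absence is not the point here. The article does state the between-group test, and that stated test is what conflicts with the design assumptions.

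The illustration rests on assumed hazards, and 65 per arm on axitinib is generous, since the Introduction itself says that fewer patients remain treatable with each line. Both stand. Smaller numbers lower the rejection rates but not the gap in proportions. The medians are components of a PFS or TTF assumption, not a forecast of exposure. Dose changes and stopping for severe AEs also make exposure depend partly on toxicity, which the model ignores.

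A reader might infer that equal toxicity will generally look like excess toxicity, or that the whole safety analysis is biased against the cytokine sequence. The documents do not support that. They give no AE onset pattern, and early AEs show little effect. First-line exposure is planned equal. Over the whole sequence the effect is diluted and mixed with real differences between cytokines and sunitinib, so the net direction is not fixed.

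**Conclusion.** The point holds for second-line therapy and for AEs whose risk continues while axitinib is given. There, the stated test confounds toxicity with duration of benefit under the trial's own assumption of 2.5 to 3.3 times longer axitinib treatment after cytokines. With equal constant hazards of 0.02 to 0.05 per month and 45 to 65 patients per arm on axitinib, the false finding of excess toxicity occurs in about 28–87% of trials, against a nominal 5% over both directions. The size depends on those assumed hazards, on exponential exposure, on using progression-based medians as a proxy for time on drug, and on which of the article's two post-cytokine figures (15.7 or 12 months) applies. The point does not extend to first line or to AEs confined to the first weeks of axitinib. It calls for a different basis for the second-line comparison and does not affect the design or the primary analysis.

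**What to change.** For second-line AEs, base the between-arm comparison on time from axitinib start to first AE, by type and for grade 3 or higher. Report the cause-specific hazard ratio with 95% CI and a log-rank test. End follow-up at axitinib discontinuation (plus any AE reporting window) or death. Keep crude proportions by grade and type as a descriptive table.

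Do not rest the conclusion on AE rates per patient-month that assume a constant hazard, since these favour the longer-exposed arm when AEs cluster early.

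The cost is a little more analysis, using AE dates and axitinib start and stop dates; no patients or visits are added. The method assumes that discontinuation is not informative for the AE in question. This is imperfect where axitinib stops because of another toxicity and should be stated with the result. Like the crude comparison, it covers only patients who start axitinib and so is not fully protected by randomization.
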